Aquatic-aerobic exercise has some advantages over other forms of exercise. These include reduced impact on articulations, less edema, increased diuresis, reduced arterial pressure, better control of body weight, less back pain, better temperature control, and lower probability of miscarriage [36]. Moreover, aquatic-aerobic exercise is not associated with risk of urinary or vaginal infections [27, 37–39]. Also, because aquatic-aerobic exercise is a group activity, compliance should be greater and there will be emotional interactions among women, and this may motivate the participants to develop healthier behaviors outside of exercise class [40, 41]. Moreover, aerobic water exercise could be an alternative to pain control during labor, reduce adverse effects such as dystocia, increase maternal satisfaction, and is likely to be readily accepted by pregnant women.

We propose a randomized clinical trial to analyze the effectiveness, safety, and cost of a moderate aerobic water exercise program on the use of epidural analgesia during labor.

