### Study population

Women will be recruited from 5 primary care centers in Mallorca, Spain. The participating primary care centers are all in a health district of a tertiary obstetric metropolitan hospital which has facilities for deliveries at 28 weeks or more. Women who are willing and able to comply with the requirements of the study will be invited to participate. Gestational age will be determined by the last menstrual period and/or by early ultrasound.

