### Sample size

The sample size calculation is based on the primary outcome measure and the primary analysis for the intention-to-treat population. Obstetric epidural analgesia in vaginal deliveries is estimated as 61% [42, 43]. Thus, we estimate a total reduction of at least 20% in the use of obstetric epidural analgesia in the intervention group based on a secondary analysis of a previous randomized clinical trial [21]. We adjusted the sample size for an estimated follow-up loss of 15% and a 0.05 two-sided level of significance (α = 5%).

Women in the control group might decide to attend other facilities to practice water exercise, swimming, or other physical activities. Thus, we increased the sample size by 15% to account for increased performance of exercise by women in the usual care group, so the final sample size will be 160 for each group (320 women total).

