### Statistical analysis

We will test for significant baseline differences in the control and intervention arms by use of descriptive analysis, with continuous variables summarized by means and standard deviations if they have normal distributions, and by medians and 25th and 75th percentiles if they have non-normal distributions.

All analyses of the effectiveness and cost-effectiveness will consider the intention-to-treat population (i.e. all randomized patients, regardless of participation in any intervention session). This approach reduces bias that may occur when participants not receiving an assigned intervention are excluded from the analysis. All tests will be two-sided, and an α-value of 0.05 will be considered statistically significant.

We will compare the proportions of women in each arm who use epidural analgesia during labor, in which the null hypothesis is no difference between the groups. We will use the Chi-squared test in bivariate analysis, and will adjust for potential confounders (if any) using a logistic regression model.

We will estimate the relative and absolute risk reduction and the number needed to treat (NNT). All estimates will include 95% confidence intervals. The NNT will be calculated as the reciprocal of the difference between the proportion of women who required epidural analgesia during labor in the intervention and control arms.

The secondary measures of effectiveness, such as reduction of instrumental delivery, reduction of Caesarean section, and post-partum depression, will be evaluated by a Chi-squared test. We will use the Mann-Whitney U test to determine if there is a statistically significant reduction of pain during labor using a VAS.

The health economic analysis will be performed by calculating the incremental cost-effectiveness ratio (ICER) at 4 weeks from delivery. We will systematically collect data on use of all resources, including inpatient care, consultations with healthcare providers, use of drugs, and laboratory tests. To measure these effects, the EQ-5D scores will be used, and quality-adjusted life years (QALYs) will be determined. The ICER will be calculated as the difference in the mean costs of the 2 groups (C_1_ – C_T_) divided by difference in the mean effects of the 2 groups (E_1_ – E_T_):$$ ICER=\frac{\overline{C_1}-\overline{C_T}}{\overline{E_1}-\overline{E_T}} $$

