A nonparametric bootstrap procedure will be used to perform the uncertainty analysis for the ICER. This procedure considers the skewness of cost data, and the covariance of costs and QALYs. To control for possible confounding and to account for clustering, an alternative procedure (Net-Benefit Regression) will also be used. Cost-effectiveness acceptability curves will be presented to show statistical uncertainty. We will determine the safety of all interventions on the “safety population” and use “per protocol analysis” to compare adverse events of patients using the Chi- squared test.

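### The primary test and intervals treat women who share exercise classes as independent; clustering is mentioned only for a supplementary cost-effectiveness regression, and the clusters are not named

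*Protocol article*

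**What the plan says.** All references are to the protocol article.

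- **Procedures, recruitment, randomization:** allocation is 1:1, of individual women, in blocks of six.
- **Study population:** "Women will be recruited from 5 primary care centers in Mallorca, Spain".
- **Intervention:** the exercise arm attends 45-minute water classes three times a week for 5 months. Under **Aquatic exercise**, controls receive standard antenatal care, with no trial classes.
- **Background:** "because aquatic-aerobic exercise is a group activity, compliance should be greater and there will be emotional interactions among women". The same sentence adds that this may motivate participants towards healthier behaviour outside class.
- **Statistical analysis, primary outcome:** "We will use the Chi-squared test in bivariate analysis", followed by logistic regression for potential confounders, if any. Relative and absolute risk reduction and NNT are to carry 95% intervals. No class term or cluster variance is named.
- **Statistical analysis, economic part:** a nonparametric bootstrap is the uncertainty analysis named first. Then: "To control for possible confounding and to account for clustering, an alternative procedure (Net-Benefit Regression) will also be used". This is the only mention of clustering, and it does not say whether class, midwife or centre is meant.
- **Sample size:** allowances are made for 15% loss and for exercise among controls (15%). No design effect is stated.

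**The concern.** This is a partially nested design: one arm is grouped after randomisation and the other is not. A Chi-squared test assumes that each woman's outcome is independent of the others'. An epidural is partly a matter of choice, and the Blinding section accepts that women in the exercise arm might change their behaviour about it. Women who meet three times a week for 5 months, under the same class leader, may come to resemble each other in that choice. The exercise arm would then carry less information than its head count suggests.

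At stake are the stated 5% error rate and the width of the intervals for the risk difference and NNT, which are the results the Discussion section hopes might change standard care. Adjusting for confounders in a logistic model does not repair this, because the fault lies in the variance.

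**Working it through.** **1. The plan's own figure: 160 per group.** The inputs in Sample size are a 61% control rate, "we estimate a total reduction of at least 20% in the use of obstetric epidural analgesia", two-sided 5%, 15% loss, and a further 15% for exercise among controls. No power is stated, so the figure cannot be reproduced with certainty. Two routes come close:
- The 20% is read as absolute and diluted by 15% (20 × 0.85 = 17 points, so 61% v 44%). At 80% power this needs 135 per arm, and 135/0.85 = 159.
- 61% v 41% at 85% power with continuity correction needs 121 per arm, and 121 × 1.15 × 1.15 = 160.

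Neither uses a clustering term. The 15% increase for exercise among controls is for contamination and is not a design effect. After 15% loss, 160 × 0.85 = 136 per arm are analysed.

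**2. Effect of clustering in one arm.** Class size *m* and ICC are not in the document, so both are assumed. With stable classes in the exercise arm only:
- Design effect in that arm: DE = 1 + (m − 1) × ICC.
- Correct/naive standard error with equal arms under the null: R = √((1 + DE)/2).
- True two-sided error of the independence test: 2 × (1 − Φ(1.96/R)).

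Worked case, m = 12 and ICC = 0.05: DE = 1 + 11 × 0.05 = 1.55; R = √(2.55/2) = 1.129; error = 2 × (1 − Φ(1.736)) = 8.3%.

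| m | ICC | DE | R | Naive SE too small by (1 − 1/R) | True error |
|---|---|---|---|---|---|
| 10 | 0.01 | 1.09 | 1.022 | 2% | 5.5% |
| 10 | 0.05 | 1.45 | 1.107 | 10% | 7.7% |
| 12 | 0.01 | 1.11 | 1.027 | 3% | 5.6% |
| 12 | 0.05 | 1.55 | 1.129 | 11% | 8.3% |
| 20 | 0.01 | 1.19 | 1.046 | 4% | 6.1% |
| 20 | 0.05 | 1.95 | 1.214 | 18% | 10.7% |

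A beta-binomial simulation (40,000 runs, 136 per arm) gives 5.9% and 7.9% for m = 10, and 6.5% and 10.9% for m = 20, close to the formula. With ICC = 0, R = 1 and the error stays at 5%.

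**3. What it does to the NNT.** For illustration, take observed rates of 61% and 41% with 136 per arm.
- Naive SE = √((0.61 × 0.39 + 0.41 × 0.59)/136) = 0.0594. The 95% interval for the difference is 8.4 to 31.6 points, NNT 3.2 to 12.0.
- With DE = 1.55 in the exercise arm, SE = √((0.2379 + 1.55 × 0.2419)/136) = 0.0671. The interval is 6.8 to 33.2 points, NNT 3.0 to 14.6.

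**4. Power once the variance is right.** Power = Φ((δ − 1.96 × SE₀)/SE₁), where δ is the difference in rates, SE₀ = √(p̄(1 − p̄)(1 + DE)/n) and SE₁ = √((p₁(1 − p₁) + DE × p₂(1 − p₂))/n), with n = 136.
- 61% v 41%: 91% without clustering, 85% at m = 10 and ICC 0.05, 78% at m = 20 and ICC 0.05.
- 61% v 44%: 80%, 72% and 64% respectively.

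**5. Centre.** Centre is shared by both arms, because women are randomised individually. Simulating 5 centres balanced between the arms, with no class effect, gave an error of 5.2%, 4.9%, 4.6% and 3.9% for centre ICCs of 0.01, 0.02, 0.05 and 0.10. Leaving centre out does not inflate the error.

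**The case against.** - **The clustering sentence is thin evidence.** It names no cluster, describes no class effect, and belongs to an additional procedure that follows an uncorrected bootstrap. This stands. A reader might infer that the authors recognised dependence between classmates and corrected for it in costs only; the text does not go that far. The point rests on the class delivery and the expected interaction, and the economic sentence shows only that clustering was in view somewhere.
- **Centre is not the problem.** This also stands, as step 5 shows.
- **Larger figures are tempting but unsupported.** Treating all exercise women of one centre as a single group (160/5 = 32) gives an error of up to 14.1% at ICC 0.05. The article does not say that classes follow centres, that groups are fixed, how large they are, or how many pools are used.
- **Randomisation protects the test if classes change nobody's epidural use.** Correct. Likeness that exists before randomisation is balanced between arms and does no harm. Inflation needs classes that do affect epidural use, differently from class to class, while averaging to no effect. The document gives no ICC for this, and the Background speaks of compliance and healthy behaviour rather than epidural choice. The size is therefore conditional.
- **An unseen analysis plan may add a class term.** Possible, and the logistic covariates are left open. But the article does fix the primary test, as one that assumes independence, and allows covariates only as confounders.

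**Conclusion.** The point holds in a conditional form. The trial groups one arm after randomisation, expects interaction within the groups, and fixes a primary test and intervals that ignore the grouping. With 10 to 12 women per stable class and an ICC of 0.01 to 0.05, all assumed, the correct standard error is 2% to 13% larger than the naive one (the naive one is 2% to 11% too small), and the true two-sided error is 5.5% to 8.3% instead of 5%. At the lower end this is minor. It grows with class size, shrinks if women move between classes, and vanishes at an ICC of zero.

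The documents do not support saying that the primary test is invalid as it stands, or that omitting centre biases it. This is an inexpensive improvement worth making, not a fatal fault.

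**What to change.** 1. Record a class group for every woman in the exercise arm. Use the class to which she was assigned, so that women who attend no session stay in the intention-to-treat analysis with a defined class.
2. Make the primary analysis a partially nested model, with a random class effect in the exercise arm only and each control as her own cluster. Alternatively, use cluster-robust standard errors with a small-sample correction.
3. Derive the risk difference and NNT, with 95% intervals, from that analysis. Keep the Chi-squared test as a sensitivity analysis.
4. In the economic paragraph, state which clusters the net-benefit regression is meant to handle.
5. A centre term is optional; it does not replace the class term.

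**Cost:** one recorded variable and changed analysis wording. Intervals become wider and some power is lost, more than slightly if classes are large or the ICC is near 0.05 (step 4 of the working). With 10 to 12 women per class there would be about 11 to 16 classes (136/12 = 11.3; 160/10 = 16). If there are fewer, either correction becomes less reliable, and the report should say so.

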### Aquatic exercise

Four sets of exercise were developed for the study, each set of exercise include exercises that looks at the full work of muscle groups and include breathing and relaxation techniques. All exercises will be performed with coordinating breathing:Warm-up out of water (5 to 7 min).Warm-up in water (5 to 10 min).Moderate aquatic exercise (20 min).Breathing and relaxation exercises (5 min).Playful exercises (5 min).

The intervention will stop if any of the followings events appear during the trial: metrorrhagia, placenta previa, premature rupture of membranes, intrauterine growth retardation, severe anemia, or any contraindications to being physically active [27].

Women in the control group will receive standard antenatal care, and the customary information given by a midwife or general practitioner. They were not discouraged from exercising on their own.

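### The adverse-event comparison is assigned to an undefined per-protocol analysis while listed harms stop the exercise programme in one arm only, so it can be biased in favour of exercise

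*Protocol article*

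**What the plan says.** The last sentence of the Statistical analysis section deals with safety. It opens with "We will determine the safety of all interventions on the “safety population" and goes on to say that the trial will "use “per protocol analysis” to compare adverse events of patients", with a chi-squared test. The article defines neither set and does not say how they relate. The only test named for adverse events is attached to the per-protocol analysis.

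The Aquatic exercise section gives the stopping rule: "The intervention will stop if any of the followings events appear during the trial: metrorrhagia, placenta previa, premature rupture of membranes", then "intrauterine growth retardation, severe anemia, or any contraindications to being physically active". For the other arm it says "Women in the control group will receive standard antenatal care", and adds that these women were not discouraged from exercising on their own.

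Earlier in the Statistical analysis section, intention-to-treat is given a limited scope: "All analyses of the effectiveness and cost-effectiveness will consider the intention-to-treat population". The reason offered is "This approach reduces bias that may occur when participants not receiving an assigned intervention are excluded from the analysis". Safety is outside that scope, although the Objectives section lists it among the secondary aims.

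**The concern.** The events that end the programme are pregnancy complications that a safety analysis would be expected to count. A woman who is stopped does not complete the classes, which run three times a week for 5 months, so she is a natural candidate for removal from a per-protocol set. No corresponding rule can remove a control woman with the same complication. She has no programme to leave, and even exercising on her own would not breach her allocation.

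If removal works this way, it depends on the outcome being compared and acts in one arm only. The groups tested are then no longer the randomised groups, and the distortion has a known direction: the exercise-arm rate falls. A true excess of events could be reduced, or an apparent protective effect could arise where there is none. The plan recognises this kind of bias when it justifies intention-to-treat for effectiveness, but does not carry the protection over to safety. The Discussion says the results might change standard care for pregnant women, so the adverse-event comparison matters.

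**Working it through.** The plan gives no figure for the safety comparison, so there is none to reproduce. The check asks how far exclusion of stopped women could move the result.

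**Inputs**
- n = 160 women per arm (Sample size section).
- r = true risk of an adverse event. Assumption: 10% in both arms. The documents give no rate.
- f = share of exercise women with an event who leave the per-protocol set. Assumption: varied, since the documents support no particular value. The lowest value, 12.5%, corresponds to a quarter of events triggering a stop and half of those women being excluded (0.25 × 0.50 = 0.125).
- Exclusions unrelated to an event are ignored, because they do not change the expected risk.

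**Formula**

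Events remaining in the exercise arm: n × r × (1 − f). Women remaining: n × (1 − r × f). Per-protocol exercise risk:

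r(1 − f) / (1 − r f)

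The control risk stays at r.

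**Equal true risk, r = 0.10**

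| f | Calculation | Exercise risk | Control risk | Relative risk |
|---|---|---|---|---|
| 0 | 0.100 / 1.0000 | 10.0% | 10% | 1.00 |
| 12.5% | 0.0875 / 0.9875 | 8.9% | 10% | 0.89 |
| 25% | 0.075 / 0.975 | 7.7% | 10% | 0.77 |
| 50% | 0.050 / 0.950 | 5.3% | 10% | 0.53 |
| 80% | 0.020 / 0.920 | 2.2% | 10% | 0.22 |

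In counts, at f = 25%, 16 expected events among 160 exercise women become 12 among 156.

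The relative risk depends mainly on f and little on r. At f = 50% it is 0.51 for r = 5% and 0.56 for r = 20%.

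**Chance of a false finding.** With 160 control women, 160(1 − r f) exercise women and a two-sided 5% test of two proportions, the chance of a significant result favouring exercise when the true risks are equal at 10% is about 11% at f = 25% and 35% at f = 50%. With no exclusion it is 2.5%.

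**True harm, control 10% and exercise 20% (assumed)**
- f = 0: relative risk 2.00, power about 71%.
- f = 25%: 0.150 / 0.950 = 15.8%, relative risk 1.58, power about 33%.
- f = 50%: 0.100 / 0.900 = 11.1%, relative risk 1.11, power about 5%.
- The excess disappears when 0.20(1 − f) = 0.10(1 − 0.20 f), that is 0.10 = 0.18 f, so f is about 56%.

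Analysing all women by assigned arm corresponds to f = 0, which returns the true relative risk in both scenarios.

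**The case against.** A reader might infer that the safety result is certain to be biased, or that the plan will conceal harm. The documents do not support either, for four reasons.

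- **The set is undefined.** Stopping on a listed event is itself part of the protocol. A woman stopped under that rule has been managed as planned and could be kept in a per-protocol set; the mechanism would then not operate. Set definitions are commonly left to a fuller document, which is not shown. This stands, and limits the claim to a bias that can arise. What does not depend on the missing definition is the stated choice to attach the adverse-event test to a per-protocol analysis.
- **Only some events trigger stopping.** The rule covers listed conditions and contraindications, not every adverse event. A 5-month programme begun at 14 to 20 weeks runs to about 36 to 42 weeks, so a late stop may follow nearly full attendance, and postpartum events come after the programme. High exclusion shares across all events are therefore hard to defend, which is why the illustration starts at 12.5%. This stands.
- **Other comparisons cover the same ground.** The Edinburgh postnatal depression scale section says complication and perinatal rates will be compared between the two groups, using the existing obstetric database. No per-protocol limit is stated there. The Safety section has all adverse events recorded and serious ones reported to the ethics committee. This stands as partial mitigation. It does not repair the adverse-event test itself.
- **An all-randomised analysis can dilute harm** by including women who never attended. This is fair, and is a reason to keep a supportive exposure-based table. It is no reason to rest the main comparison on programme completers.

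**Conclusion.** The point holds in conditional form. The plan assigns its only named adverse-event test to an undefined per-protocol analysis, and the stopping rule can act in the exercise arm only. If stopped women are treated as non-compliant, the comparison can be biased in favour of exercise, by the kind of exclusion the plan cites as its reason for intention-to-treat.

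The effect ranges from modest (relative risk 0.89 when the truth is 1.00) to severe (0.22), according to the share excluded. That range rests on an assumed 10% event risk, on assumed exclusion shares, and on the listed stopping events being counted as adverse events. The primary outcome, the sample size and the intention-to-treat analyses of effectiveness and cost-effectiveness are unaffected.

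**What to change.** Replace the safety sentence in the Statistical analysis section with wording such as:

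> The main comparison of adverse events will be by assigned arm in all randomised women with any follow-up. Events that lead to stopping of the exercise programme, and events after it is stopped, will be counted. An as-treated table (exercise women with at least one session) will be supportive and will retain women whose programme was stopped. Any per-protocol table will be supportive only, with its set defined in advance.

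If the term safety population is kept, define it to match one of these sets.

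The cost is about one sentence in the protocol or analysis plan. No new data are needed, because all adverse events are already to be recorded on case report forms. The downside is that women who never attended may slightly dilute a harm signal, which the as-treated table addresses. The stopping rule itself is unchanged.

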## Abstract

**Background:**

Epidural analgesia during labor can provide effective pain relief, but can also lead to adverse effects. The practice of moderate exercise during pregnancy is associated with an increased level of endorphins in the blood, and this could also provide pain relief during labor. Aerobic water exercises, rather than other forms of exercise, do not negatively impact articulations, reduce edema, blood pressure, and back pain, and increase diuresis. We propose a randomized controlled trial (RCT) to evaluate the effectiveness and safety of a moderate water exercise program during pregnancy on the need for epidural analgesia during labor.

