### Objectives

The main objective of this study of women with uncomplicated pregnancies is to compare a standard antenatal care program with a program of aquatic-aerobic exercises of moderate intensity on the use of epidural analgesia during labor. The secondary objectives are to test the effect of the water exercise program on use of epidural analgesia before 6-cm cervical dilation, dystocic delivery, induction of labor, subjective satisfaction with the experience of childbirth, pain perception during the first stage of labor, duration of labor (first and second stages), and postpartum depression, and to assess the safety and cost-effectiveness of the aquatic-aerobic exercise program.

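### The only between-arm method named for the safety objective is a Chi-squared test of adverse events, which at this sample size would more likely miss than detect a doubling of a harm with a control rate of about 6% or lower

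*Protocol article*

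**What the plan says.** The Abstract gives the trial's purpose as to "evaluate the effectiveness and safety of a moderate water exercise program during pregnancy on the need for epidural analgesia during labor". The Objectives section lists, among the secondary aims, "to assess the safety and cost-effectiveness of the aquatic-aerobic exercise program".

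The last part of the Statistical analysis section says how safety will be handled. The sentence begins "We will determine the safety of all interventions on the" safety population, and then adds a per-protocol analysis "to compare adverse events of patients using the Chi- squared test". The same section sets the error rate for everything: "All tests will be two-sided, and an α-value of 0.05 will be considered statistically significant".

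Sample size is tied to efficacy alone: "The sample size calculation is based on the primary outcome measure and the primary analysis for the intention-to-treat population". The result is "so the final sample size will be 160 for each group (320 women total"). No expected harm rate and no power for safety is stated.

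Two other statements bear on the point. In the paragraph on risk reduction and number needed to treat for epidural use, the Statistical analysis section says "All estimates will include 95% confidence intervals". The Safety section provides for recording of adverse events, causality assessment by the investigators and reporting of serious outcomes to the ethics committee.

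**The concern.** A test of difference can show that one arm has more harm. It cannot show that the arms are alike: its only result on the favourable side is a p-value above 0.05, and in a small trial that is the expected result for an uncommon harm whether or not the harm has increased. The article says that safety will be determined, and the one tool it names for comparing the arms cannot do this for uncommon events at this sample size.

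The participants are women with low-risk pregnancies, and the Discussion foresees that conclusive results might change standard antenatal care. A statement of no significant difference in adverse events, without an estimate and interval beside it, would tell readers little about how large an excess of harm the data leave open.

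**Working it through.** **Inputs from the article.** 160 women per arm; 15% expected loss, so 160 × 0.85 = 136 per arm; 1:1 allocation; Chi-squared test at two-sided 0.05; epidural rate 61% in controls.

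**Assumed.** The article gives no harm rates. I used control rates p₁ from 1% to 10%, with p₂ = 2p₁ in the exercise arm.

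**The plan's own figure.** The article does not state its power, so 160 cannot be strictly reproduced. The usual formula is n = [1.96·√(2p̄(1−p̄)) + z_β·√(p₁(1−p₁)+p₂(1−p₂))]² / (p₁−p₂)². If the 20% reduction is absolute (61% to 41%), it gives 97, 111 and 130 per arm at 80%, 85% and 90% power. At 85%, 111/0.70 = 159, close to 160. A relative reduction (61% to 48.8%) needs 260 per arm at 80% power before any inflation. So 160 fits a 20-point difference in a common event. For that difference, power is about 95% at 160 per arm and 91% at 136.

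**Power for a doubled harm.** The normal approximation is power = Φ{[|p₂−p₁| − 1.96·√(2p̄(1−p̄)/n)] / √[(p₁(1−p₁)+p₂(1−p₂))/n]}.

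For 5% versus 10% with n = 160:
- p̄ = 0.075, and 1.96·√(2·0.075·0.925/160) = 0.0577
- √[(0.0475+0.09)/160] = 0.0293
- (0.05 − 0.0577)/0.0293 = −0.263, so power = 0.396

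The approximation is rough for rare events. The table therefore uses exact enumeration of two binomials with the uncorrected Pearson test.

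| Control → exercise | Power, 160 per arm | Power, 136 per arm | Miss rate (160 / 136) |
|---|---|---|---|
| 1% → 2% | 10% | 8% | 90% / 92% |
| 2% → 4% | 17% | 14% | 83% / 86% |
| 3% → 6% | 25% | 21% | 75% / 79% |
| 5% → 10% | 39% | 35% | 61% / 65% |
| 6% → 12% | 47% | 42% | 53% / 58% |
| 7% → 14% | 54% | 48% | 46% / 52% |
| 10% → 20% | 71% | 65% | 29% / 36% |

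Power passes one half between control rates of 6% and 7% at 160 per arm, and just above 7% at 136. With the Yates correction it is lower (5% to 10%: 32% and 26%).

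**Women needed per arm for 80% power**, from the first formula: 2,319 (1% to 2%), 1,141 (2% to 4%), 435 (5% to 10%) and 199 (10% to 20%).

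**What an interval would add.** These are invented counts with 160 per arm, using the Newcombe score interval for the risk difference.
- 5 versus 10 women with an event: p = 0.19; difference 3.1 points, 95% CI −1.8 to +8.3. The test reports no difference, while the interval leaves open an excess of 8 points.
- 5 versus 5: p = 1.0; difference 0, 95% CI −4.4 to +4.4. Even equal counts do not exclude a doubling, which would be +3.1 points on a rate of 3.1%.

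**The case against.** **The stronger reading is not in the text.** A reader might infer that a p-value above 0.05 will be reported as proof that the programme is safe. The article states no such rule, and the Discussion's remark about changing care is conditional and concerns pain control. This stands: the point is what the named test can support, not what the investigators will claim.

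**Intervals may be intended.** Taken literally, the sentence on 95% intervals covers all estimates, and the section on the Edinburgh scale says that rates of pregnancy complications and perinatal outcomes will be compared between groups. It would therefore be too firm to say that no confidence limit is planned for any harm. But the interval sentence sits between two sentences about epidural use, and the adverse-event sentence names a test and no estimate to which an interval could attach.

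**Other safety handling exists.** Causality review and ethics reporting deal with individual events. They do not estimate an excess between arms.

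**Detail may sit elsewhere.** A tolerable excess for harms could be in the full protocol or analysis plan, so its absence here is not part of the point. The article does name a method, however, and that choice can be judged.

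**Low power for rare harms is normal** in a trial sized for efficacy, and the article never claims otherwise. True; that is a reason not to rest the safety determination on a significance test.

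**The wording is loose.** Grammatically, the test may belong to the per-protocol comparison only. If so, it would use no more women, and probably fewer, so power would not be better.

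**Conclusion.** The point holds in limited form. The Chi-squared test is the only between-arm inferential method the article names for its safety objective. At 136 to 160 women per arm, a doubling of a harm would more likely than not be non-significant when the control rate is about 6% or lower. The statement does not extend to common harms: at 10% versus 20% the test detects the doubling in 65% to 71% of trials. A non-significant result could therefore not support a safety conclusion for uncommon harms.

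This rests on assumed harm rates, a doubling as the increase of interest, and the uncorrected test. It does not rest on any claim that the investigators will treat non-significance as safety, or that intervals for harms have been ruled out.

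**What to change.** Reword the safety sentence in the Statistical analysis section as follows:

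- For adverse events, and for the maternal, neonatal and resource-use outcomes already collected that reflect harm, report the number of women (or infants) with an event per arm and the risk difference with a two-sided 95% confidence interval, using a score or exact method where events are rare.
- Base the safety statement on the excess that the interval does or does not exclude.
- Keep the Chi-squared p-value as descriptive.
- Add a sentence such as: a non-significant difference in adverse events will not be taken as evidence of safety, because the trial was not sized for harms.

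This needs no new data or participants, only a change of wording and a few table columns. The cost is a weaker conclusion: for uncommon harms the trial will probably have to report that a relevant excess cannot be excluded. The change does not improve the ability to detect harm; it makes the remaining uncertainty visible.
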